### Interventions

#### Hyperbaric oxygen therapy

Within 2 weeks of enrolment, each study participant is placed into the hyperbaric chamber, but only those patients allocated to active HBOT receive 90 minutes of oxygen at 2.4 ATA with the patients breathing 100% oxygen when inside the chamber. Those patients randomized to placebo will be compressed on air to 0.3 ATA (10 feet) and kept at that level. The patient will remain in the chamber for the remainder of the placebo treatment breathing normally. At the end of the treatment, after a short period of enhanced ventilation (to simulate surfacing) the chamber will be opened. Patients enter the chambers 5 days per week for approximately 6 weeks for a total of 30 treatments. At the end of the 6 week treatment phase, patients enter a 6-week follow-up phase.

#### Dressing changes

Based on the characteristics of the wound, dressings will be changed as required (at a minimum of 2 dressing changes per week). Wound care is standardized throughout the entire study to several different dressing types (e.g. silver, simple gauze, and alginate, collagen/oxidized cellullose) dependent on the type of the wound (e.g. dry, wet, and intermediate). The very wet wounds receive daily dressing changes as required by standard of care. Clinical signs of infection are noted and antibiotic therapy initiated if required and swabs obtained. Referral for debridement of the wound occurs if necessary.

### Data collection

Data to evaluate the efficacy of HBOT are collected at screening, baseline, and weekly throughout the 6-week treatment phase, weekly throughout the 6-week follow-up phase at 30 and 52 weeks. At the end of the 6-week follow-up phase (i.e. week 12), the patient is sent to the participating vascular surgeon for an amputation evaluation. If the patient's wound has not healed, the wound care physician, in consultation with the vascular surgeon will then decide if further HBOT or other treatment is indicated. Once all study data for each patient are received, the randomization assignment may be revealed. Data are collected via interview, self administrated questionnaire, physical and biological measurements. Data collection instruments and the study timeline are summarized in Table 1. All instruments used have been previously validated.

**Table 1 T1:** Schedule of study assessments and evaluations

			Treatment Phase		Follow-up Phase		Long-Term Follow-up	
			
Clinical Assessments, Testing and Investigations	Screening and Randomization	Baseline	Weeks 1 to 6	End of Treatment	Weeks 6 to 12	End of Follow-up	Week 30	Week 52
Suitability for HBOT	X							

Electrocardiogram	O							

Pulmonary Function Testing	O	X						

Audiogram	O							

Chest X-ray	O							

X-ray of affected limb	O	X						

Nuclear bone scan	O							

Vascular Exam	X	O	O	O	O	X		

History & Physical		X						

Demographics		X						

Treatment Details		X	X					

Wound Classifications (Wagner, Bates)	X	X	X		X			

Wound Measurements		X	X		X			

Wound Characteristics		X	X		X			

Digital Photograph of wound		X	X		X			

Dressing Changes	X	X	X		O	O		

Concomitant Meds		X	X		X			

Assess for Infection	X	X	X		X			

Mobility Status		X	X		X			

Adverse Events		X	X		X		X	X

Outcome Assessment	X	X	X		X			

Unblinding		O	O	O	O	O		

Laboratories	X	X		X		X		

Resource Utilization		X	X		X		X	X

**Quality of Life**:								

SF-36		X		X		X		

EQ-5D		X		X		X	X	X

DFS-SF		X		X		X		

x = required o = optional

SF-36: Short-Form 36; EQ-5D: EuroQoL 5D; DFS-SF: Diabetic Foot Ulcer Scale - Short Form

### Primary Outcome

The primary outcome in this study is freedom from having, or meeting the criteria for, a major amputation (below knee amputation, or metatarsal level) up to 12 weeks after initiation of treatment. The decision to amputate is made by a vascular surgeon and by meeting any of the following criteria:

1. Persistent deep infection involving bone and tendons (antibiotics required, hospitalization required, pathogen involved);

2. Ongoing risk of severe systemic infection related to the wound;

3. Inability to bear weight on the affected limb;

4. Pain causing significant disability.

### Secondary Outcomes

#### 1) Wound healing

Measures of wound healing include difference in wound measurements (i.e. depth, length, width and extent of surface area) using: a digital photograph; reduction in Wagner Classification Score; Bates-Jensen Wound Assessment score; proportion of wounds closed on or before 12 weeks; and time to healing (days).

##### Digital Photographs for Healing Assessment

Using a digital camera with PictZar^® ^CDM Software, digital images of the wounds are captured and downloaded to a computer. Once downloaded to a computer, PictZar^® ^CDM Software is used to make various surface measurements on the wound photograph (i.e. depth, length, width, area, circumference and volume). The software provides a method of calibrating digital images based on a calibration strip placed on the skin adjacent to the wound. Photographs are used for comparison to assess the degree of ulceration.

##### Wagner Scale

The foot ulcer classification system used in this study was described and popularized by Wagner [38]. In the Wagner system, the natural history of dysvascular foot breakdown is divided into six grades ranging from Grade 0 (preulcer) to Grade 5 (amputation required). The system is similar to an ordinal scale denoting ranked order, allowing for nonparametric data analysis. Grade is determined based on depth of the skin lesion and the presence or absence of infection and gangrene.

##### Bates-Jensen Wound Assessment Tool

The Bates-Jensen Wound Assessment Tool (Barbara Bates-Jensen ^© ^2001) [39], is a validated wound assessment tool that evaluates 13 wound characteristics with each item scored on a 1-5 scale. A total score is obtained by adding all individual scores and the results are plotted on the Wound Status Continuum. Higher total scores indicate a more severe wound status.

#### 2) Effectiveness

Maintenance on therapy (discontinuation rates) and secondary prevention interventions (confounding variables that may influence primary outcome such as diabetes control) are collected.

#### 3) Safety

Major morbidity (e.g. infection requiring hospitalization, acute coronary syndrome, renal failure); wound interventions during study (debridement, surgery); complications related to HBOT (seizure, pulmonary syndromes, vision disturbance, middle ear or sinus problems); and all cause mortality are recorded on the case report forms.

#### 4) Healthcare resource utilization

All healthcare resources used by study patients during the course of the study are documented (e.g. wound dressing materials, healthcare provider visits; inpatient hospital admissions; complex continuing care/rehabilitation; drug therapy; mobility assistive devices, etc.).

#### 5) Quality of life

Diabetic foot ulcers are associated with pain, discomfort and immobility, which could lead to anxiety, depression, and isolation. As a result, one of the secondary objectives of this study is to measure any changes in HRQL in the two treatment groups. Three different instruments are utilized: 1) a generic quality of life instrument - Short-Form 36; 2) a preference-based or utility measure - EuroQoL 5D (EQ-5D); and 3) a disease-specific questionnaire - Diabetic Foot Ulcer Scale - Short Form. Self-assessment will be performed at baseline, 6 weeks, and 12 weeks in order to monitor the progress or decline of the patient through their own interpretation. Only the EQ-5D will be administered at weeks 30 and 52.

#### 6) Cost effectiveness of HBOT

The final objective of this study is to assign cost values to the healthcare resource utilization data in order to determine the incremental cost per amputation avoided and the incremental cost per quality-adjusted life-year (QALY) gained associated with the treatments.

## Early Discontinuation

If a patient's wound heals during the treatment phase, they discontinue the HBOT treatment visits but continue their weekly visits until week 12. Dressing changes and prevention care plans are put in place and wound evaluation visits include the documentation of healthcare resource utilization, quality of life measurements, and any relevant clinical information.

Alternatively, if amputation criteria are met during the treatment phase, the outcome is recorded and efforts made to maintain wound care as per protocol until amputation procedure can be done or if systemic infection or ascending infection then immediate referral to surgery. Healthcare resource utilization is collected weekly and quality of life is collected for these patients as per protocol (i.e. 6 and 12 weeks).

If a patient discontinues the assigned treatment due to inability to tolerate or unwilling to comply with therapy but is still willing to remain in the study, the patient is provided standard wound care. Wound evaluation visits are completed when possible.

If a patient needs to temporarily discontinue treatment due to a medical illness, infection in the wound where HBOT cannot be continued, or complications of the wound, this is considered a temporary interruption. Once the patient has recovered, they may begin a new HBOT treatment regimen. All patients who have temporarily had their treatment interrupted will be followed for all regular clinical wound evaluation (Table 1).

## Statistical Analysis

### Data Analysis

Baseline variables will be evaluated for balance between the two groups using the Student's t-test for unpaired data for the comparison of continuous variables and the Pearson's chi-squared test to compare categorical variables.

For the primary outcome of rate of, or criteria for, major amputation, the chi-squared test will be used. Additionally, a relative risk will be estimated for the major amputation rates in each arm and multivariable logistic regression analysis of major amputations will be performed using a number of covariates.

All test instruments for the various secondary outcomes will be scored according to the recommendations for the particular tests, with missing values handled in an appropriate fashion (e.g., prorated sum, average) and corrections for repeated measures will be applied where appropriate. Scores for any patients who die prior to the end of study from causes directly related to their wound (e.g. sepsis) are considered to have required an amputation. Patients who die from other causes are eliminated from further analyses due to lack of follow-up data but the outcome recorded. When patients are unwilling to complete a follow-up visit or are lost to follow-up we will use chi-squared analysis to determine whether there is imbalance between the treatment groups with respect to loss of follow-up.

The extent of healing of the ulcers will also be assessed by measuring the ulcer surface area from the digital photographs. Since it is a continuous variable, data will be tested for normality and analyzed as appropriate with t-test or non-parametric test if required.

All analyses will be based on the "intention-to-treat" principle. Per-protocol analyses will also be conducted.

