### Sample Size

A comprehensive search and review of the electronic medical literature databases was conducted to identify randomized controlled trials of HBOT versus standard treatment to collect data to calculate the sample size required for the current study. Sample size calculations were to be based on evidence from published randomized controlled trials comparing the efficacy, in terms of rates of major amputation, of HBOT versus standard treatment for patients with various wound classifications using the Wagner's Ulcer Classification Grade [38].

Of the 348 citations obtained, only one study [16,19] reported the rates of major amputation for Wagner's classifications necessary for the calculation of sample size for this study given that it was decided a priori that patients with Wagner Grades of 2,3 or 4 would be recruited into the study. Based on these data, the expected event rate in the standard care group was 39.29% and 11.54% in the HBOT group and using a two-sided test for equality.

Using these data, it was estimated that a total of 94 patients were needed for this study (47 patients per treatment group). However, due to the fact that subjects might leave the study for a variety of reasons (e.g. loss to follow-up, non-compliance with treatment, or death), the sample size was adjusted to accommodate for this. It was assumed that there was a likely dropout rate of 20%. This assumption would require a total of 118 subjects, or 59 subjects in each treatment group (i.e., 94/(1-0.20) = 118).

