## Disscussion

This study has been designed to address some of the shortcomings of previous research, namely this study will be the largest and first double-blind randomised controlled trial to evaluate the efficacy of HBOT for the prevention of major amputations in diabetic patients with non-healing ulcers of the lower limb. The study uses a remote randomization system to protect concealment of allocation and proposes that the primary comparative analyses be conducted on an intention-to-treat basis in accordance with the 2010 CONSORT statement [40].

Participants are followed up for a 12-month period in order to capture the impact of HBOT treatment in both the immediate (i.e. 12 weeks) and longer term. This two-arm study, with 49 participants per group, should provide sufficient power to detect a meaningful difference in amputation. If successful, this intervention may lead to substantial and important changes in the management of diabetes patients at risk of amputation due to non-healing ulcers of the lower limb.

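### Ulcer surface area is compared by a test chosen from the data and without its baseline value; one pre-specified baseline-adjusted analysis would be more precise at no cost in data

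*Protocol article*

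**What the plan says.** The Data Analysis section fixes the method for ulcer surface area, measured from digital photographs: "Since it is a continuous variable, data will be tested for normality and analyzed as appropriate with t-test or non-parametric test if required". It names no covariate for this comparison.

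Table 1 (Data collection) marks wound measurements and Wagner classification as required at baseline, in weeks 1 to 6 and in weeks 6 to 12. The Wound healing section lists the outcome as a difference in wound measurements. It does not say whether this means change from baseline within a patient or a difference between arms at follow-up.

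For major amputation the same section says: "For the primary outcome of rate of, or criteria for, major amputation, the chi-squared test will be used". It adds a relative risk and says that "multivariable logistic regression analysis of major amputations will be performed using a number of covariates". The covariates are not named. Randomisation and Blinding describes blocks of four and mentions no stratification by Wagner grade.

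**The concern.** Letting a normality test choose between a t-test and a rank test makes the question answered depend on the data. One branch estimates a difference in means; the other compares distributions by rank. The choice is also largely predictable: areas cannot be negative, large ulcers are likely to skew them, and every ulcer that heals contributes a zero. The article expects some to heal, since it counts wounds closed by 12 weeks and describes patients who heal during treatment.

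The second weakness is that ulcers of very different sizes at entry are compared as if nothing were known about their starting size. That variation goes into the error term although the trial already measures it. At stake is the precision of a healing result that will be read beside the amputation result in a trial of 118 patients.

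**Working it through.** **Inputs from the article.** Planning rates and sidedness: "the expected event rate in the standard care group was 39.29% and 11.54% in the HBOT group and using a two-sided test for equality". Evaluable size: "a total of 94 patients were needed for this study (47 patients per treatment group". Dropout 20%, giving 118.

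**Assumed, because the article does not give them.** Two-sided alpha 0.05; correlation rho of 0.3 to 0.8 between baseline and follow-up area; equal SDs at the two times; grade shares of 30/40/30% for Wagner 2/3/4; log odds ratio per grade of 0 to 1.5.

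**1. The plan's own figure.** With the unpooled normal formula and 90% power (inferred, since the article states no power):

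n = (1.960 + 1.282)² × (0.3929×0.6071 + 0.1154×0.8846) / (0.3929 − 0.1154)² = 10.51 × 0.3406 / 0.0770 ≈ 46.5, so 47 per arm.

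94/0.80 = 117.5, so 118. The stated size reproduces, and this point does not disturb it. Continuity-corrected 80% power (45) and arcsine 90% power (48) also come close, so the 90% is not certain.

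**2. Ulcer area, linear-model variances** (SD σ, n per arm):
- final value: 2σ²/n
- change from baseline: 2σ²·2(1−rho)/n
- covariance adjustment: 2σ²(1−rho²)/n

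Adjusted against final value the ratio is 1−rho². Adjusted against change it is (1−rho²)/[2(1−rho)] = (1+rho)/2. The power columns take an effect for which the final-value test has 80% power.

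| rho | Ratio to final value | Ratio to change | Power, change | Power, adjusted |
|---|---|---|---|---|
| 0.3 | 0.91 | 0.65 | 65.8% | 83.6% |
| 0.5 | 0.75 | 0.75 | 80.0% | 89.9% |
| 0.7 | 0.51 | 0.85 | 95.1% | 97.5% |
| 0.8 | 0.36 | 0.90 | 99.3% | 99.7% |

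Adjustment has the smaller variance in every row, whichever way the outcome is read.

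**3. Skewed area, simulated.** Lognormal areas, 47 per arm, 4,000 runs, with a Shapiro-Wilk pre-test in each arm (the article names no test).
- Pre-test route on follow-up area: about 77% power at rho 0.3, 0.5 and 0.7.
- Pre-test route on change in area: 47%, 59% and 79%.
- Covariance analysis of log area: 83%, 89% and 97%.

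Part of the gap to the change route comes from the log scale rather than from adjustment. The simulation has no zeros, so it shows direction and rough size only. The rank-based version was not simulated.

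**4. Major amputation, simulated.** Chi-squared test against a Wagner-stratified Cochran-Mantel-Haenszel test, 47 per arm, 6,000 runs, at the planning rates.

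| Log odds ratio per grade | Chi-squared | Stratified | Difference (points) |
|---|---|---|---|
| 0 | 89.7% | 88.9% | −0.8 |
| 0.5 | 89.0% | 89.0% | 0.0 |
| 1.0 | 89.5% | 91.2% | +1.8 |
| 1.5 | 89.3% | 93.4% | +4.2 |

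Each power has a simulation standard error of about 0.4 points (√(0.9×0.1/6000) = 0.0039). With an assumed HBOT rate of 18%, the chi-squared test has about 63% to 65% and the stratified test 63% to 72%.

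**The case against.** The strongest defence is that two-sample tests on a randomised comparison are valid, that area is one of several healing measures, and that its outcome may already be change from baseline, in which case baseline area is used after all. The validity and the secondary rank stand. The third argument narrows the gain without removing it: the ratio to a change score is still 0.65 to 0.90. It is also fair that 1−rho² belongs to linear covariance analysis, while the zeros favour a rank-based method whose gain was not computed.

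A reader might go further in several ways that the article does not support.

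- **That the primary analysis is deficient because the chi-squared test ignores Wagner grade.** The test's error rate already allows for chance imbalance, an adjusted logistic model is planned in the same paragraph, and naming its covariates is commonly left to the analysis plan. Choosing planning rates for grades 2 to 4 defines the population; it does not establish a risk gradient within those grades.
- **That adjustment is worth 1.6 to 2.8 times the patients.** This is 1/0.64 to 1/0.36. It needs a final-value comparison and a correlation of 0.6 to 0.8, and the article states neither.
- **That an odds ratio beside a relative risk misleads.** They are 0.20 and 0.29 at the planning rates, but they are different measures, and the relative risk is planned explicitly.
- **That baseline p-values will select covariates.** The article says only "Baseline variables will be evaluated for balance between the two groups using the Student's t-test", and gives balance as the purpose.
- **That QALYs are wrongly left unadjusted.** The article states nothing wrong there, and such detail is usually left to the analysis plan.

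**Conclusion.** The point holds for ulcer area. The method is stated, not merely left open: a data-driven choice between two tests, without the baseline value that the trial is required to collect. The effect measure is therefore not fixed in advance, and precision is lost at any non-zero correlation against a final-value test and at any correlation below 1 against a change score. For rho of 0.3 to 0.8 the variance falls by 9% to 64% in the first case and by 35% to 10% in the second. The size depends on a correlation that the article does not give; the direction does not.

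For major amputation there is no error. Naming Wagner grade in the planned adjusted model is a small gain in pre-specification, worth about -1 to +4 points of power at the planning rates under assumed grade effects. Overall this is an efficiency improvement to a secondary outcome, and it leaves the sample size and the primary test unaffected.

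**What to change.** Replace the sentence on normality testing with one analysis, for example:

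*Ulcer surface area at week 12, with healed ulcers counted as zero, will be compared between arms by rank-based analysis of covariance with baseline area and baseline Wagner grade as covariates. No preliminary test of normality will be used.*

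State the effect measure to be reported with it.

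As a minor addition, name baseline Wagner grade as a covariate in the planned adjusted analysis of major amputation. Keep the chi-squared test as the primary test.

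The cost is analysis wording and a little programming. No new data are needed, since Table 1 already requires both covariates at baseline. Because Data collection allows a patient's assignment to be revealed once that patient's data are in, the change should be dated and recorded before anyone compares area by arm.

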### Subgroup Analysis

There are no planned subgroup analyses anticipated. Only primary and secondary outcome measures will be analyzed. However, all of the variables which are found to be important predictors of amputation and adverse outcomes, will be used for stratifications for post-hoc analyses.

### Health Economic Evaluation

An economic evaluation will be conducted in order to assess the cost-effectiveness of HBOT plus standard wound care compared to wound care alone. The analysis will be based upon patient-level outcome and resource use data from the trial. Two cost-effectiveness outcomes will be measured: 1) cost per major amputation avoided; and 2) the cost per QALY gained. Modeling techniques will be used to extend the time horizon beyond the duration of the trial. A third-party payer perspective (i.e. Ontario Ministry of Health) will be taken in the evaluation.

Healthcare resource utilization over the duration of the trial is measured for each patient. A number of different cost components are being considered: HBOT treatment; follow-up wound care visits; inpatient admissions; general practitioner visits; specialist visits; other allied healthcare professional visits (e.g. chiropodists, physiotherapists); and mobility assistive devices (e.g. wheelchairs, walkers). The cost per HBOT treatment will be based upon the Judy Dan Wound Care Centre operating budget. The cost for nurse wound care will be based upon the average hourly nursing wage in Ontario. For patients in the active HBOT plus standard care arm, treatment costs will include both HBOT and wound care nurse costs. For patients in the standard wound care arm, treatment costs will not include HBOT costs.

Follow-up resource use data will be assessed at the completion of HBOT treatment (week 6), weeks 12, 30 and 52. Appropriate unit costs will be applied to the resource use data to estimate follow-up costs for each patient. Unit costs will be derived from a number of sources including the Ontario Case Costing Initiative database and the OHIP Schedule of Benefits.

QALYs for each treatment arm will be based upon utilities measured over the duration of the trial. Uncertainty of cost-effectiveness results will be estimated using non-parametric bootstrap techniques and presented using cost-effectiveness acceptability curves.

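### The rule eliminating patients who die of non-wound causes is not lifted for the economic evaluation; read as written, it drops these deaths from the QALYs although utility after death is 0

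*Protocol article*

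**What the plan says.** In the protocol article, Health Economic Evaluation names two cost-effectiveness outcomes: cost per major amputation avoided and cost per QALY gained. On the second it says "QALYs for each treatment arm will be based upon utilities measured over the duration of the trial". The utility instrument is the EQ-5D, given at baseline and at weeks 6, 12, 30 and 52 (Quality of life section and Table 1). No value is stated for time after death. The section adds that resource use is measured for each patient and that a model will extend the horizon beyond the trial.

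Deaths are handled only under Data Analysis, in the paragraph that opens "All test instruments for the various secondary outcomes will be scored according to the recommendations for the particular tests". It contains two rules:

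- Wound-related deaths: patients who die "from causes directly related to their wound (e.g. sepsis) are considered to have required an amputation".
- All other deaths: "Patients who die from other causes are eliminated from further analyses due to lack of follow-up data but the outcome recorded".

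The same section ends with "All analyses will be based on the 'intention-to-treat' principle". Under Safety, "all cause mortality are recorded on the case report forms".

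**The concern.** The reason given for eliminating non-wound deaths is the lack of follow-up data. For an amputation outcome or a wound score that reason can at least be argued. For a QALY it fails, because the value after death is known: utility is 0 from the date of death. Excluding the patient replaces a known low value with, in effect, the average of those who remain.

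The rule is worded without limit, and it stands in the paragraph on the secondary-outcome instruments. The EQ-5D is one of these, and cost-effectiveness is itself listed as the sixth secondary outcome. Nothing in the economic section lifts the rule.

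The other rule does not help. Counting a wound-related death as an amputation settles an amputation outcome but gives no usable EQ-5D value.

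At stake is one of the two stated cost-effectiveness results, in a trial started on an advisory committee's recommendation for evidence on which to decide about HBOT and reported to the Ministry whose perspective the evaluation takes. Both arms' mean QALYs would be too high. A difference between arms in non-wound mortality would not reach the incremental QALY. On the literal reading, costs accrued before those deaths would be lost as well.

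**Working it through.** The article gives no QALY total, utility value, death rate or cost-effectiveness ratio, so there is no stated figure to reproduce. The check reads the rules together and then illustrates the size.

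**Reading the rules together**

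1. QALYs use utilities measured in the trial. None can be measured after death.
2. Non-wound deaths leave further analyses. No analysis is excepted.
3. All analyses follow intention-to-treat, so every randomised patient should count in the arm assigned.

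Rules 2 and 3 cannot both hold for the QALY. If rule 2 is followed, rule 1 offers nothing to put the deaths back.

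**Size over 52 weeks**

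All inputs are assumptions:

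- u, utility while alive: 0.5 to 0.7, the same in both arms and in patients who later die
- m, share of an arm dying of non-wound causes: 5%, 10% or 15%
- t, fraction of the year lived before death: 0.25 to 0.75

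Mean QALY with death counted as 0: u × [(1 − m) + m × t].
Mean QALY with those deaths dropped: u.
Overstatement of the arm mean: u × m × (1 − t).

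- m = 5%: from 0.5 × 0.05 × 0.25 = 0.006 to 0.7 × 0.05 × 0.75 = 0.026
- m = 10%: from 0.5 × 0.10 × 0.25 = 0.0125 to 0.7 × 0.10 × 0.75 = 0.0525

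Error in the incremental QALY: u × (difference in m) × (1 − t). Dropping the deaths returns a difference of 0 in place of:

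- 10% v 5%: 0.006 to 0.026; central case 0.6 × 0.05 × 0.5 = 0.015
- 15% v 5%: from 0.5 × 0.10 × 0.25 = 0.0125 to 0.7 × 0.10 × 0.75 = 0.0525
- equal mortality: 0, so no bias in the increment

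The sign follows the arm with more deaths. With 59 patients per arm, 10% v 5% is about 6 v 3 deaths (5.9 v 2.95).

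**The case against.** The strongest reply is that the death rule belongs to the clinical analyses. The economic evaluation has its own subsection, uses patient-level data and measures resource use for each patient; nowhere does the article say that the death rule governs it. A zero utility for death is also the kind of convention that an article leaves to a fuller plan, like the EQ-5D tariff or interpolation.

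Part of this stands. Silence about the zero alone would be no finding. But the article is not silent: it states an exclusion, without limit, for a reason that is wrong for this outcome. Measuring resource use for each patient describes data collection, and the rule itself separates recording a death from analysing the patient.

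A second reply is that the elimination may apply only from the date of death. Pre-death data and costs would then be kept, and the QALY would be right if nothing accrued afterwards. It would still be overstated if that time were treated as missing and filled in or averaged over. The text does not settle which.

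It is also fair that the increment is biased only if non-wound mortality differs, and the article gives no reason to expect that HBOT changes it.

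A reader might infer more than the text supports:

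- *The QALYs and costs describe survivors only, and any mortality effect is lost.* Wound-related deaths are kept as amputation events and so enter cost per amputation avoided. All-cause mortality is recorded, and how the model treats mortality is not described.
- *Wound-related deaths are valued like living amputees.* No utility is assigned to them. Were an assumed amputee utility of 0.4 to 0.6 used for the rest of the year, the overstatement per such death would run from 0.4 × 0.25 = 0.10 to 0.6 × 0.75 = 0.45 QALY, but the article does not say this is done.
- *The extrapolation model starts from figures without these deaths.* Its starting point is not stated.

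**Conclusion.** The point holds in a limited form. As written, the elimination of non-wound deaths reaches the QALYs and, read literally, the costs. It conflicts with intention-to-treat and treats a known value as missing. The rule for wound-related deaths leaves their EQ-5D value undefined.

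Arm means are overstated whenever non-wound deaths occur. The incremental QALY is wrong only if non-wound mortality differs between arms: by about 0.006 to 0.026 QALY at 10% v 5%. That range rests wholly on the assumed utility, mortality and timing of death. It is tempting to express it as a share of the QALY gain expected from fewer amputations. The article does not support such a percentage: it gives no utility loss for amputation, and an amputation-only comparator leaves out any gain from wound healing.

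The finding concerns the economic evaluation. Correcting how deaths count in the amputation comparison would not repair it, since that sets no utility to 0 and restores no costs.

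**What to change.** Reconcile Data Analysis with Health Economic Evaluation by adding to the latter, or to the analysis plan, wording to this effect:

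- All randomised patients enter the economic evaluation in the arm assigned.
- EQ-5D utility is 0 from the date of death, from any cause, to week 52.
- Costs accrued up to death are kept.
- The death rules in Data Analysis do not apply to QALYs or costs.
- The bootstrap resamples these complete patient records.

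The cost is a few sentences. All-cause mortality is already recorded, so the only extra item needed is the date of death, if the case report form does not already hold it. No further visits or patients are required. The QALY figures will be slightly lower. This wording exempts the economic evaluation only; the conflict between the elimination rule and intention-to-treat in the other analyses remains and has to be settled separately.
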